## Abstract

**Introduction::**

Wake up stroke starts in sleep and is a more common form of ischemic stroke. At present, it is still controversial whether wake up stroke can be treated with thrombolytic therapy. Therefore, this study will combine imaging techniques to assess the onset time of wake up stroke patients, and to analyze the imaging characteristics of wake up stroke patients and patients suitable for thrombolytic therapy within the time window.

**Methods/design::**

This study will be a single-blinded, randomized controlled trial with 2 parallel groups. It will be conducted at North China University of science and technology affiliated hospital.

**Discussion::**

There is no consistent conclusion about the pathogenesis of wake up stroke. Wake up stroke is more likely to manifest as small vessel disease. The incidence of wake up stroke patients is relatively high, and the effectiveness and safety of intravenous thrombolysis under the guidance of multimode imaging therapy in wake up stroke need to be further explored by prospective, large-scale studies.

**Trial registration::**

ClinicalTrials.gov, ChiCTR2000034402, Registered on 05 July 2020

## Introduction

1

The patient was normal when he fell asleep at night, but after waking up, he developed stroke symptoms.^[1]^ This phenomenon was defined as wake up stroke (WUS). Due to the inability to accurately determine the actual time of onset of this part of patients, according to the criteria of stroke diagnosis and treatment guidelines, this part of patients are often excluded from recombinant tissue plasminogen activator (rt-PA) treatment. WUS is relatively common clinically, accounting for about one-quarter of patients with new-onset ischemic stroke,^[2]^ but the statistical data obtained by different studies are quite different. A population-based study in the United States in 2005 found that^[3]^ nearly 58,000 WUS patients in the United States were seen in the emergency department in 2005. The CASPR report^[4]^ the data of 11 hospitals in 5 different areas of California surveyed by it showed that the proportion of WUS accounted for about 8% of ischemic stroke, other states such as Houston is about 6.4%, Boston is about 27%.^[5,6]^ A 4-year study in the UK found that the incidence of WUS is about 25% (135/545).^[7]^ The stroke registration from Canada found that WUS accounted for 13.5%.^[8]^ Lausanne, Switzerland, reported that the incidence of WUS was as high as 33.1%.^[9]^ In the Asian region, Japan and South Korea accounted for 9.7% and 27.8% of WUS occurrences.^[10,11]^ China currently lacks epidemiological surveys on WUS. Although it is currently difficult to draw a uniform ratio from the existing statistical data, we can find that WUS is more common clinically. Data from clinical and imaging studies indicate that the onset time of most patients with ischemic stroke is between 6:00 and 12:00 in the morning,^[12]^ showing a peak in the morning. Therefore, scholars speculate that there may be a considerable proportion of WUS patients whose onset time is close to awakening, and there is still the possibility of thrombolytic therapy. In recent years, multimodal imaging techniques have been used to evaluate the ischemic penumbra after cerebral ischemia in WUS patients, thereby guiding thrombolytic therapy.^[13]^ There have been some clinical studies based on multimodal imaging techniques to guide WUS thrombolytic therapy and found that a considerable portion of WUS patients can benefit from thrombolysis,^[14]^ but most of these studies are relatively small samples and are observational studies. The use of rt-PA thrombolytic therapy in the early stage is one of the most effective treatment methods for acute cerebral infarction, but due to the limitation of time window, the proportion of patients benefiting is not high. Although the European Acute Stroke Collaboration Study extended the time window for intravenous thrombolysis, the proportion of thrombolysis in China is still <2%.^[15]^ Whether WUS can be used for thrombolytic therapy is still controversial. Therefore, this study will combine the imaging technology to assess the onset time of WUS patients, and analyze the imaging characteristics of WUS patients and patients within the time window suitable for thrombolytic therapy.^[16]^ This study aimed to observe the efficacy of intravenous thrombolysis in WUS patients.

## Methods/design

2

### Study design and settings

2.1

This study will be a single-blinded, randomized controlled trial with 2 parallel groups. It will be conducted at North China University of Science and Technology-affiliated hospital. This protocol was written and based on Standard Protocol Items: Recommendations for Interventional Trials guidelines. If they agree, they will sign an informed consent form. Only those participants who read and agree to the protocol and who sign the informed consent form will take part of the study, following the schedule described in Figure 1.

**Figure 1 F1:**
[figure not shown]
SPIRIT figure for the schedule of enrollment, interventions, and assessments. mRS = modified RanKin scale, NIHSS = National Institutes of Health Stroke Scale, SPIRIT = Standard Protocol Items: Recommendations for Interventional Trials.

### Ethical

2.2

Before this clinical trial begins, we will submit the research protocol to the ethics committee for review. We will not recruit participants until the ethics committee agrees. This study will be approved by the Ethics Committee of North China University of Science and Technology-affiliated hospital. It will be conducted in accordance with the protocol. The rules of confidentiality will be respected.

### Patients participating in the trial

2.3

#### Participants

2.3.1

We will continuously include patients with ischemic stroke who are hospitalized in the Affiliated Hospital of North China University of Technology. We will refer to the diagnostic criteria for ischemic stroke developed by the Neurological Branch of the Chinese Medical Association.

#### Inclusion criteria

2.3.2

Time of onset: last appeared to be normal until symptoms will be found <12 hours and >4.5 hours;The patient was found to be awake or witnesses found neurological deficits;NIHSS score ≥4 points;No changes or early changes are insufficient to the one-third distribution area of the middle cerebral artery;DWI/FLAIR imaging performance mismatch (DWI imaging and FLAIR imaging);All other indications for intravenous thrombolysis;Patients with large vessel occlusion are treated with endovascular treatment. The treatment principles refer to “Chinese Expert Consensus on Intravascular Treatment of Acute Ischemic Stroke.”

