#### Treatment solutions

2.5.2

Patients in the defined time-onset group will be given intravenous thrombolysis. The awakening group performs multimodal magnetic resonance imaging (MRI) screening (DWI and FLAIR) on the basis of meeting the pre-set conditions. If the MRI indicates that the DWI-FLAIR does not match, intravenous thrombolytic therapy will be given; if the MRI shows DWI-FLAIR matching, it will be given general treatment. Intravenous thrombolysis uses rt-PA. One-time dosage is 0.9 mg/kg, and the maximum dose does not exceed 90 mg. First, a 10% dose of intravenous bolus was given, and the rest of the dose continued to be infused intravenously for a total of 60 minutes. Thrombolysis is completed in the intensive care unit of the neurology department. During the thrombolysis process, the patient's consciousness and changes in limb muscle strength are closely observed. During this period, we will monitor patients’ vital signs, blood oxygen saturation, and give them treatments such as free radical scavenging and stable plaque. Recheck the computed tomography (CT) of the brain after 24 hours. If no intracranial hemorrhage is found, antiplatelet aggregation treatment (0.1 g oral aspirin tablets) should be given, and acupuncture and rehabilitation should be given after the condition is stable. Patients in the WUS group without thrombolysis received aspirin 300 mg orally as soon as possible after admission, and then changed to 100 mg/day. Other treatment methods will be the same as those of thrombolytic therapy.

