#### Safety evaluation after thrombolysis

2.6.1

The occurrence time, treatment measures, and results of various adverse events such as intracranial hemorrhage, skin, gums, and digestive tract in patients undergoing thrombolytic therapy are recorded by specialized personnel. The safety of thrombolytic therapy is mainly evaluated by the incidence of intracranial hemorrhage. During thrombolysis, if there is headache, vomiting, and other suspected intracranial hemorrhage or other parts of the bleeding, stop thrombolysis immediately. At the same time, review the head CT. If there is no symptom of appeal, the head CT is reviewed 24 hours after thrombolysis. The significant deterioration of nerve function caused by intracranial hemorrhage (increased NIHSS score ≥4 points) will be considered as symptomatic intracranial hemorrhage.

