## Discussion

3

Intravenous thrombolytic therapy for ischemic stroke in the ultra-early stage has been proved to be an effective treatment in most randomized trials. However, ultra-early intravenous thrombolysis has a strict treatment time window (onset time <4.5 hours). Exceeding this treatment time window will increase the incidence of symptomatic intracranial hemorrhage, and severe cases may be life-threatening. WUS starts in sleep and is a more common form of ischemic stroke. Its incidence rate can be as high as 25%.^[17]^ Since patients or witnesses cannot provide accurate time of onset, the start time of stroke is still “normal at last.” Therefore, even if the patient or eyewitness finds out, the prescribed time window has already been exceeded. However, some recent research results prove that the original method does not seem appropriate. The study by Kim et al^[18]^ also focused on patients with WUS and stroke patients with unknown onset times during the day without witnesses. He found that nearly half of WUS patients will be immediately awake as soon as clinical symptoms appeared. Roveri et al^[19]^ divided the study subjects into 2 groups, the WUS group and the intravenous thrombolysis group within 3 hours of onset. Early CT manifestations will be applied to the early CT score of the Alberta Stroke Project (ASPECTS), and it was found that regardless of the risk factors and stroke severity Or the ASPECTS score is very close between the 2 groups. There was no statistically significant difference in the early CT scan ASPECTS scores between the 2 groups, indicating that the ischemic event of WUS patients occurred shortly before awakening or awakened as soon as the disease occurred. The author also pointed out that the prognosis of patients in the intravenous thrombolysis group was significantly better than that in the WUS group. The most representative epidemiological evaluation of WUS comes from a 2-center study of 1853 patients with ischemic stroke, including 273 WUS patients. The results show that compared with non-WUS patients, the incidence of WUS patients older age and higher NIHSS score on admission. However, if the time window is not considered, 35% of the patients are suitable for thrombolytic therapy. Then, if we can more accurately assess the onset time of WUS patients, a large number of patients will benefit from thrombolytic therapy. The study found that the mismatch of DWI/FLAIR has a high specificity and sensitivity for the judgment of patients within 3 to 4.5 hours. Thomalla et al^[20]^ observed 543 patients within 4.5 hours of onset. Under the field strength of 1.5 T, the specificity of DWI/FLAIR mismatch judgment of stroke patients within 4.5 hours of onset was as high as 78%. Morelli et al^[21]^ collected 27 WUS patients and 143 non-WUS patients and received intravenous thrombolysis. The results showed that the proportion of patients with mRS ≤1 point was 36.4%. The author mentioned in the conclusion that the selected WUS patients are suitable for intravenous thrombolysis. This study is based on the previous study, and has a purposeful choice for WUS patients who are given thrombolytic therapy. The imaging findings are consistent with DWI/FLAIR mismatch. In summary, we speculate that the selected WUS patients are safer to use intravenous thrombolytic therapy, which is expected to improve the patients’ early efficacy and long-term prognosis. However, whether the statistically significant benefits can be obtained remains to be observed by expanding the sample size. There is no consistent conclusion about the pathogenesis of WUS. WUS is more likely to manifest as small vessel disease. Male patients with sleep apnea are more likely to have WUS, and frequent snoring may be one of the mechanisms of WUS pathogenesis.^[22,23]^ The incidence of WUS patients is relatively high, and the effectiveness and safety of intravenous thrombolysis under the guidance of multimodality imaging treatment of WUS need to be further explored by prospective, large-scale studies.

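### The time criterion stops at symptom discovery, so rt-PA can be given to patients certainly more than 4.5 hours from onset

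*Protocol article*

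**What the plan says.** Section 2.3.2 (Inclusion criteria) of the protocol article sets the time criterion as "last appeared to be normal until symptoms will be found <12 hours and >4.5 hours". The next criterion covers how the deficit comes to notice (on waking or through a witness) and has no time attached. A later item adds "All other indications for intravenous thrombolysis", without hours. The exclusion criteria in section 2.3.3 contain no time limit.

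Section 2.5.2 (Treatment solutions) sends the awakening group to MRI "on the basis of meeting the pre-set conditions", again without hours, and then fixes the trigger for treatment: "If the MRI indicates that the DWI-FLAIR does not match, intravenous thrombolytic therapy will be given".

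The Abstract explains the purpose of imaging: "this study will combine imaging techniques to assess the onset time of wake up stroke patients". The Discussion (section 3) says that "the mismatch of DWI/FLAIR has a high specificity and sensitivity for the judgment of patients within 3 to 4.5 hours". It also says that "ultra-early intravenous thrombolysis has a strict treatment time window (onset time <4.5 hours" and that going beyond this window raises symptomatic intracranial haemorrhage. Section 2.6.1 names the main safety measure: "The safety of thrombolytic therapy is mainly evaluated by the incidence of intracranial hemorrhage".

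**The concern.** In a wake-up stroke trial, two intervals determine how old the lesion can be at treatment: last normal to discovery, and discovery to rt-PA. The criterion limits only the first. The second limits lesion age from below, because symptoms already exist at discovery. Once it exceeds 4.5 hours, no uncertainty about onset is left for imaging to resolve.

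The article justifies mismatch as a marker of recent onset. In a patient whom the clock already places beyond 4.5 hours, mismatch cannot do that job, and a positive scan is a false positive for the stated purpose. The Discussion's argument that selected patients are safer to thrombolyse rests on the same inference and does not extend to them. What is at stake is the risk of intracranial haemorrhage, which is the trial's main safety measure and which the article itself says rises beyond the window.

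**Working it through.** The article states no figure to reproduce here, so the check is interval logic.

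**Inputs**
- Bounds of 4.5 and 12 hours, with the clock ending at discovery: section 2.3.2.
- Treatment on mismatch, with no maximum delay stated: section 2.5.2.
- Treatment window of less than 4.5 hours from onset: section 3.
- Clock times below are illustrations, not data from the article.

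**Notation.** S is the time from last normal to discovery, and D the time from discovery to rt-PA, both in hours. Onset lies between last normal and discovery, so lesion age at rt-PA lies in [D, S + D]. If D > 4.5, the whole range lies above 4.5, and no such patient can be within the window, whatever the onset distribution.

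**Two readings of the criterion**
- Literal: 4.5 < S < 12. D does not appear, so every D above 4.5 is admitted.
- Interval meant to run to treatment: 4.5 < S + D < 12. D > 4.5 is still admitted whenever S < 12 − 4.5 = 7.5. D can then run up to 12 − S, which is 7 h for S = 5, 6 h for S = 6 and 5 h for S = 7.

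**Cases**

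| Last normal, discovery, rt-PA | S | D | S + D | Literal | To treatment | Lesion age (h) |
|---|---|---|---|---|---|---|
| 00:00, 05:00, 11:00 | 5 | 6 | 11 | met | met | 6 to 11 |
| 23:00, 06:00, 11:30 | 7 | 5.5 | 12.5 | met | not met | 5.5 to 12.5 |
| times not specified | 8 | 5 | 13 | met | not met | 5 to 13 |
| 23:00, 03:00, 06:00 | 4 | 3 | 7 | not met | met | 3 to 7 |

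The first case decides the point. It qualifies on both readings, and its lesion is at least 6 − 4.5 = 1.5 h past the window. The second and third depend on the literal reading. The fourth shows a separate side effect of the literal wording: an early waker who may be within 4.5 h of onset, and who is outside the standard window counted from last normal (7 h at treatment), fails the lower bound because S is only 4 h.

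**With a limit of D ≤ 4.5.** The lower end of the lesion-age range is then at most 4.5 h, so no treated patient is certainly past the window. The upper end is below 12 + 4.5 = 16.5 h if the 12-hour bound ends at discovery, or below 12 h if it ends at treatment.

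**The case against.** The strongest reply is that a journal article condenses a fuller protocol. The references to pre-set conditions and to other thrombolysis indications may point to a limit that is not reproduced, and Figures 1 and 2 are not shown. Stating one interval does not prove that no second clock exists. Investigators who call the window strict would hardly treat patients they know to be outside it, so the other-indications item could be read as importing a limit from onset or discovery.

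Part of this stands: an unseen source could hold a limit. But the article does state its time rule, with two bounds and an end point, so the objection is to what it fixes. The word other sets the remaining indications apart from the time criterion, and no hours are given. An ordinary 4.5-hour window counted from last normal would bar every patient the literal criterion admits. A limit counted from waking or discovery would therefore have to be written down, and in the text shown it is not.

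Three further points deserve an answer.
- The wording is imprecise, and the interval may have been meant to run to treatment. That narrows the gap but does not close it, as the first case shows.
- The Introduction mentions imaging of the ischaemic penumbra as a guide to treatment. That is general background. The trial selects on DWI-FLAIR mismatch, which the article justifies by onset time.
- The Discussion cites a specificity of 78% for mismatch, so most patients beyond 4.5 hours would not be treated. Taken as reported, that still leaves 100% − 78% = 22% showing mismatch. Imaging reduces the problem without removing it.

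It is also true that nothing in the article shows how often such long delays would occur.

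**Conclusion.** The concern holds. Followed as written, the eligibility and treatment rules allow rt-PA in patients who are certainly more than 4.5 hours from onset, where the article's own reason for relying on mismatch cannot apply. Above 4.5 hours from discovery, 0% of patients can be within the window. This is admitted without restriction on the literal reading, and for any S below 7.5 hours if the interval runs to treatment.

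The only assumption in the arithmetic is that onset does not come after discovery. The conclusion is limited to the text shown. The share of the trial population affected is unknown, and none is claimed. The point should be fixed, with medium confidence given the loose wording and the missing figures.

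**What to change.** Amend the time criterion in section 2.3.2 in three respects:

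- Require rt-PA to start within 4.5 hours of waking or symptom discovery.
- State that the lower bound of more than 4.5 hours runs from last normal to treatment, so that the wording does not exclude patients who wake early but are outside the standard window.
- State whether the 12-hour bound ends at discovery or at treatment, and keep its value.

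This changes one criterion and uses times already known when treatment is decided. Some late arrivals become ineligible, but none of them can be within 4.5 hours of onset, so no in-window patient is lost. The added limit loosens neither reading of the 12-hour bound.

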#### Grouping method

2.4.2

We will be divided into awakening stroke group (wake group whose morbidity is not exact) and ischemic stroke group (the group clarifying the time of onset) according to whether the onset time of the patient is clear. The awakening group is divided into the awakening group with thrombolytic therapy and the awakening group without thrombolysis according to whether they receive thrombolytic therapy.

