#### Laboratory examination

2.4.3

For patients who meet the inclusion criteria, blood routine (white blood cells, hemoglobin, platelets, etc.), biochemistry (liver function, kidney function, myocardial enzymes, blood lipids, and so on), blood coagulation (activated partial thromboplastin time, blood coagulation) time, plasma prothrombin time, and so on), conventional electrocardiogram, chest radiograph and other examinations.

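### DWI/FLAIR mismatch is both an entry criterion and the rule for giving rt-PA, so the untreated wake-up group has no eligible members

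*Protocol article*

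**What the plan says.** Section 2.3.2 (Inclusion criteria) is a single list with no labels by group. Two of its items matter here: "DWI/FLAIR imaging performance mismatch (DWI imaging and FLAIR imaging") and "All other indications for intravenous thrombolysis". It also requires an interval of more than 4.5 and less than 12 hours between last being normal and discovery of symptoms, and it sends large vessel occlusion to endovascular treatment. Section 2.4.3 (Laboratory examination) refers to the list without restriction: "For patients who meet the inclusion criteria".

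Section 2.4.2 (Grouping method) plans three groups: known-onset stroke, wake-up stroke with thrombolysis and wake-up stroke without it. The two wake-up groups are separated "according to whether they receive thrombolytic therapy".

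Section 2.5.2 (Treatment solutions) performs MRI in wake-up patients "on the basis of meeting the pre-set conditions", a term it does not define. It continues: "If the MRI indicates that the DWI-FLAIR does not match, intravenous thrombolytic therapy will be given"; and "if the MRI shows DWI-FLAIR matching, it will be given general treatment". The control regimen is spelled out: "Patients in the WUS group without thrombolysis received aspirin 300 mg orally as soon as possible after admission", followed by a lower daily dose.

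Section 2.1 describes a randomized trial with two parallel groups, and section 2.7 has sealed envelopes, opened after eligibility is settled, decide the grouping.

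**The concern.** One imaging result serves as both the gate into the study and the switch for treatment. If mismatch is needed to enter and mismatch also triggers rt-PA, nobody who enters is left for the untreated wake-up group.

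The Introduction gives the aim as observing the efficacy of intravenous thrombolysis in wake-up stroke, and the contrast that speaks to it is treated against untreated wake-up patients. Staff who follow both sections have no controls. To obtain controls they must break either the entry criterion or the treatment rule, and which one they break decides what the comparison means.

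If match patients are let in as controls, treatment coincides completely with mismatch. The Discussion uses mismatch as a marker of onset within 4.5 hours and cites a specificity as high as 78%. The untreated group would then tend to be the later-onset group, and a poorer outcome there could be mistaken for a benefit of rt-PA.

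**Working it through.** The protocol gives no figure to reproduce on this point, so the check is to set the rules side by side.

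**Step 1. Each MRI result against each rule, for wake-up patients**

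| MRI result | Entry (2.3.2) | Treatment (2.5.2) | Eligible and assigned to no thrombolysis? |
|---|---|---|---|
| Mismatch | eligible if other items are met | rt-PA | no |
| Match | not eligible | general treatment, aspirin | no |

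The count is 0 of 2.

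**Step 2. Other routes into the untreated group**

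- *Contraindication to rt-PA.* The list requires all remaining indications for thrombolysis, so it leaves no stated ground for withholding rt-PA from an eligible patient.
- *Large vessel occlusion.* These patients go to endovascular treatment, which is not the aspirin regimen of section 2.5.2.
- *Grouping by treatment received (2.4.2).* An eligible mismatch patient could land in the untreated group, but only by departing from section 2.5.2.
- *Envelope (2.7).* An envelope could send a mismatch patient to control, again only against section 2.5.2.

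**Step 3. Does the answer depend on whom the list covers?**

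| Scope of 2.3.2 | Empty by rule | What still conflicts |
|---|---|---|
| (a) All participants | untreated wake-up group, 1 of 3 | 2.3.2 against 2.5.2; observed-onset patients also excluded |
| (b) All wake-up patients | untreated wake-up group, 1 of 3 | 2.3.2 against 2.5.2 |
| (c) Thrombolysed wake-up patients only | none, 0 of 3 | treated are 100% mismatch and untreated 100% match, so imaging and not the envelope sets the group, against 2.1 and 2.7 |

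At least one stated rule must change in 3 of 3 scopes.

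**Step 4. Secondary point, under scope (a) only.** For a patient whose onset was observed, take the interval from last normal to discovery as about 0 hours (an assumption; the protocol gives no value). That fails the required interval of more than 4.5 hours, yet sections 2.4.2 and 2.5.2 make known-onset patients a thrombolysed study group.

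**The case against.** The best reply is that scope (c) was intended. The list reads largely as a set of conditions for thrombolysis in an extended window, and its reference to all other indications suggests that the items before it are indications too. Section 2.3.1 separately describes consecutive inclusion of hospitalized ischemic stroke patients. Section 2.5.2 places MRI after the pre-set conditions, so mismatch may not be one of them, and the Discussion ties mismatch to the wake-up patients who are treated. The exclusion of known-onset patients under scope (a) is itself a sign that the list was not meant for everyone. On this reading match patients are the controls and no group is empty.

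That reading has real support, and the empty-group result does depend on scope. But section 2.3.2 does not state the restriction, and section 2.4.3 treats the list as general. If it is adopted, the untreated group has no inclusion criteria of its own, and imaging assigns treatment in a trial described as randomized. This is a different conflict from the empty group, but it means the reading does not make the protocol consistent.

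Two further points stand in part. The flow chart and the schedule figure are not available here and might show where MRI falls relative to entry; a figure could clarify the intent, but the written criteria would still need correcting. And an empty control group would not defeat every purpose: section 2.8 includes before-after tests, and the Introduction also names a comparison with patients within the time window. Neither replaces the planned untreated wake-up comparison.

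**Conclusion.** The concern holds. Followed as written, sections 2.3.2 and 2.5.2 leave the untreated wake-up group with no eligible members: 0 of 2 MRI results, and 1 of 3 planned groups empty if the list covers all participants or all wake-up patients. If it covers only thrombolysed wake-up patients, no group is empty, but treatment and imaging status coincide completely and the randomization claim fails.

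The counts describe the rules and do not predict what staff would do in practice. The conclusion rests on the visible text. It must be fixed before recruitment, because the choice made determines what the main wake-up comparison can show.

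**What to change.** Split section 2.3.2 into common and group-specific criteria. Limit the 4.5 to 12 hour last-normal interval to wake-up patients, and give the known-onset group a criterion of onset under 4.5 hours, in line with the Discussion. Then use mismatch in one role only:

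- **Option (i).** Remove mismatch from entry, keep it as the treatment rule in section 2.5.2, and state in sections 2.1 and 2.7 that the wake-up comparison is not randomized. This is wording only and changes no assigned treatment. Section 2.2 says the protocol is still to go to the ethics committee, so it can be done before submission. The cost is the claim of a randomized wake-up comparison. It does not remove the confounding of rt-PA with mismatch; it makes the groups fillable and the claim accurate.
- **Option (ii).** If randomization is intended and the ethics committee accepts it, keep mismatch as a wake-up entry criterion and replace the match/mismatch rule in section 2.5.2 with envelope allocation. This separates treatment from imaging status but is a redesign: it withholds rt-PA from some mismatch patients, drops match patients and needs a fresh check of recruitment.

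Option (i) is the minimum needed for the protocol to be followed as written.
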